## Abstract

Frailty has become a major challenge for health systems, but it also presents a window of opportunity to fight disability through preventive strategies focused on the detection and treatment of frailty across all care settings. However, no systematic strategies for screening and early detection are currently available in clinical practice. This project aims to identify clinical and biological phenotypic clusters that drive progression through the different stages of frailty, and to describe the underlying mechanisms of the trajectories leading to disability and potential treatment interventions. In addition, the Frailty Trait Scale 5 (FTS5) will be validated as a practical tool for implementation in both primary care and hospital settings. A prospective, population-based cohort (CohorFES) will be established for frailty phenotyping. A CIBERFES Biobank will also be created to store blood and urine samples from CohorFES participants for future research. Demographic and clinical history data, anthropometric measurements, the PREDIMED questionnaire, peripheral blood biochemical variables, and metabolomics data will be collected at baseline and annually until participants develop frailty. Cluster partition models (k-means and hierarchical clustering) will be used to group individuals with similar deficits and characteristics (frailty phenotypes). Then, by using pre-established criteria (gap and silhouette), the proposed clustering solution (belonging to given clusters) will be evaluated. We will also assess, in a longitudinal manner, the emergence and accumulation of deficits over time, identifying subgroups with more rapid progression. The results will be used to define and compare clusters and progression trajectories. Finally, frailty phenotypes and patient clusters will be correlated with health outcomes such as healthcare utilization (primary and secondary care), hospital admissions, and mortality. Information on clinical and biological phenotypic clusters involved in the progression of frailty may help identify potential therapeutic targets to improve the management of these patients. In summary, from a research perspective, this project aims to improve our understanding of the interindividual variability in clinical trajectories that lead to frailty, dependence, and ultimately, death.

**Protocol Registration:**
NCT06965972 (date 05/02/2025)

## Introduction

Frailty is one of the main challenges of the 21st century and a top priority for national and international organizations such as the WHO (World Health Organization) and the European Parliament. This has placed it as one of the top priorities on the European Commission’s biomedical research agenda [1,2]. Frailty is characterized by a physiological state of increased vulnerability and decreased resilience to stressors (i.e., diseases, external agents, drug tolerability and toxicity) due to the combined effect of the aging process and some chronic diseases, leading to a final phase of dependency and disability, with a significant impact on quality of life, consumption of healthcare and social resources, hospitalization, and death [2].

The importance of frailty detection and management is well recognized, given its reversibility [3], the associated healthcare costs [4], and its clinical implications [5]. In contrast to the abundance of data from non-clinical settings, there is a lack of robust data in clinical settings, where frailty prevalence is highest and the risk of serious adverse consequences is greatest [6]. Therefore, there is an urgent need to improve the detection and diagnosis of frailty, its trajectories, and the determinants of these trajectories, depending on the patient’s characteristics (whether or not associated with sarcopenia, cognitive impairment, or various chronic diseases).

While the different categories of frailty syndrome (robust, frail, pre-frail) are well defined and characterized epidemiologically [7,8], there is little data on the functional pathways between these diagnostic categories (and, notably, disability), especially in clinical cohorts. This is particularly striking given that one of the most relevant factors associated with poor frailty outcomes is hospitalization [9].

Another key issue is the implementation of an easy-to-use tool to identify frailty and related factors in all outpatients. The Frailty Trait Scale (FTS) has demonstrated the ability to detect frailty in some clinical settings (Acute Care Geriatric Units, Geriatric outpatient clinics, and Primary Care) and has good predictive capacity for adverse outcomes (death, incident disability, decline in SPPB score, falls, and hospitalization) at 6, 12, and 18 months [10,11]. However, the full version of the FTS, composed of 12 items, takes about 15 minutes to complete, making it impractical in routine clinical settings where time is limited.

With this in mind, a shorter version comprising only 5 items (the so-called FTS5) was developed [12]. This version offers promising results, maintaining the sensitivity to detect small changes shown by the full FTS. The variables that make up the FTS5 (gait velocity, grip strength, BMI, PASE, and balance) can also be incorporated into electronic tools, such as the electronic frailty index (eFI) [13]. The use of such electronic tools has proven useful not only in hospital care but also in routine primary care practice. Furthermore, it facilitates the measurement of adverse outcomes, including falls, delirium, disability, care home admission, hospitalization, and mortality, as recently demonstrated [14].

In this regard, several clinical guidelines have been proposed for the early identification and prevention of frailty in the elderly [15–17]. These guidelines aim to address one of the major healthcare challenges: the growing aging population and the increasing incidence of chronic diseases. In particular, in 2022, the Frailty and Falls Prevention Working Group updated a “consensus document on the prevention of frailty in the elderly,” approved by the Interterritorial Council of the Spanish National Health System. This document highlights the importance of early diagnosis and the need for interventions within the healthcare system, especially in primary care [15]. This aspect is particularly important because frailty is not an inevitable consequence of aging; instead, it represents a dynamic and potentially reversible condition, with early stages offering the greatest opportunity for recovery.Therefore, early detection and diagnosis of frailty are essential not only for quality of life but also for the efficient use of healthcare and social resources.

Our overarching goal is to identify critical subgroups of individuals at risk of progressing from robustness to pre-frailty and frailty, and from there to later stages, as well as the pathways mediating this trajectory in community-dwelling Spanish subjects.

Within this conceptual framework, and considering the limited data available in clinical settings regarding frailty diagnosis, trajectories, and prognosis, the main goal of this project is to establish a real-life, clinical, prospective cohort (CohorFES). This cohort aims to identify clinical and biological phenotypic clusters contributing to progression through the different stages of frailty and to elucidate the underlying mechanisms that ultimately lead to disability.

Additionally, the project will validate the Frailty Trait Scale 5 (FTS5) as a practical and easily applicable tool for use in both primary care and hospital settings.

Finally, a multicenter biobank will be created within the CIBERFES consortium to store blood and urine samples from CohorFES participants, ensuring their availability for future research initiatives.

## Materials and methods

### Study design and setting

We will stablish a multicentered cohort, the CohorFES, a prospective and observational study based on population. The study is registered in clinicaltrials.Gov as observational study: NCT06965972 (date 05/02/2025). Patients will be recruited from the start of the project and will be followed annually throughout the study.

Participants are women and men over 65 years old who attend outpatient clinics at participating centers, including the Hospital del Mar Research Institute in Barcelona, the Hospital General Universitario Gregorio Marañón in Madrid, the Complejo Hospitalario Universitario de Albacete in Albacete, the Hospital General Universitario de Ciudad Real in Ciudad Real, the Fundación del Hospital Nacional de Parapléjicos in Toledo, and the Hospital Universitario de Getafe in Madrid.

### Participant selection for cohort study

Inclusion criteria consisted of women and men older than 65 years who had provided signed written informed consent. Exclusion criteria included patients in a critical end-of-life situation or with a Barthel Index score below 60, patients who had been hospitalized for any illness within the previous six months, and patients diagnosed with and currently receiving treatment for any type of cancer, with the exception of non-melanoma cutaneous cancer.

### Sampling procedure

Individuals who are visited at participating centers and meet the inclusion criteria are invited to participate in the study. Participants are enrolled consecutively after providing written informed consent. All individuals included in the CohorFES are also invited to participate in the Biobank, after informed consent was obtained. Serum, plasma, buffy coat, and urine samples will be collected at baseline (V0) and annually thereafter.

### Sample size

The sample size calculation for this study is based on index data from the Toledo Healthy Aging Study. Since the prevalence rates of frailty, as well as the progression of frailty syndrome, are expected to be higher in the clinical population than in the general population, these estimates can be considered conservative and therefore offer an additional safety margin to achieve sufficient statistical power.

Frailty rates are estimated from subjects who have a negative FTS5 that later develop frailty, which was 0.075 (7.5%). The ratio of exposed/ unexposed was 1008/196 (ratio of negatives vs. positives), that is 5.1. The minimum relative risk value (RR) to be detected is estimated taking as an interest variable “incident frailty” (stage transition marker) for which OR of the different estimates range between 1.78 and 5.4 and therefore we adopt a RR conservative to detect of 2. Finally, the loss of follow-up rates is estimated at 10%.

With these data, sample size was calculated using a Poisson distribution approach, appropriate for the analysis of event rates. The calculation was based on the expected incidence rate of the outcome, the anticipated rate ratio between groups, a two-sided significance level of 0.05, and a statistical power of 80%. Therefore, accepting an Type 1 error of 0.05 and a Type II error of 0.2 in a two-sided contrast, 215 subjects in the exposed group and 1075 in the unexposed group are needed to detect a factor of risk with a minimum relative risk value of 2.

### Study schedule

This is a prospective study with long-term follow-up, where patients will have a visit every 12 months for all study procedures. We anticipate continuing follow-up until 1,500 patients are included, with a minimum follow-up duration of one year per participant.

The recruitment period will run from January 2, 2021, to December 31, 2027. Data will be collected throughout the entire study period, which is expected to conclude in 2030. At that point, all data will be analyzed and the results will be reported.

The recruitment process comprises a preselection visit to assess inclusion and exclusion criteria and to inform the participant about the study, followed by a baseline visit during which all study variables will be collected and written informed consent will be obtained. Each participant will complete a minimum of three study visits. These will include the baseline visit (V0) and 2 years of follow-up (V1 at 1 year of follow-up and V2 at two years of follow-up). Follow-up visits will be conducted every 12 months until the end of the study; during these visits, the same clinical variables collected at baseline will be reassessed, and biological samples will be collected. A final visit may take place upon completion of the study, participant withdrawal, or the diagnosis of frailty or death.

### Variables

All variables and biological samples will be obtained at baseline and at all subsequent visits until the end of the study or the patient’s withdrawal (Fig 1).

**Fig 1 pone.0345101.g001:**
[figure not shown]
SPIRIT schedule enrollment.

#### Main variables.

The main variables are based on the evaluation of the frailty score:

**Frailty Trait Scale 5 items (FTS5**): 1.- walking speed test, 2.- grip strength, 3.- Physical Activity, 4- Body Mass Index (BMI), and 5.- progressive Romberg test. Each of the 5 domains scores from 0 (the lowest) to 10 (the highest), being 50 the highest score possible in this tool. Participants with a score higher than 25 were considered as frail [12].**Fried phenotype**: 1.-weight loss, 2.-exhaustion, 3.-weakness, slowness, and 4.-low physical activity. Frailty status was defined as robust or nonfrail (individuals who did not meet any criteria), prefrail (1 or 2 criteria met), and frail (≥3) [7].**Electronic Frailty index (eFI):** It is a validated instrument that operationalizes the cumulative deficit model of frailty, using routinely collected electronic health record data (36 items) to quantify frailty and stratify older adults according to their risk of adverse outcomes such as hospitalization, institutionalization, and mortality [13].

These three frailty parameters will be compared to each other to validate whether the FTS5 could be used as a practical and easy-to-apply tool in both primary care and hospital settings.

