Finally, the identified frailty phenotypes and patient clusters will be examined in relation to clinically relevant health outcomes, including the utilization of health care services in both primary and secondary care settings, hospital admissions, biomarker profiles, and mortality. Appropriate regression models will be used depending on the outcome of interest, and results will be reported using effect estimates with corresponding 95% confidence intervals. Where applicable, analyses will account for follow-up time and relevant covariates. These analyses will enable the assessment of the prognostic and clinical relevance of the identified frailty phenotypes and trajectories.

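### The contrast that sets the sample size (FTS5-positive versus negative on incident frailty) has no stated analysis, and the stated FTS5 validation leans partly on agreement with a scale that shares three of its five domains

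*Protocol article*

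**What the plan says.** The Introduction sets the aim: "the project will validate the Frailty Trait Scale 5 (FTS5) as a practical and easily applicable tool for use in both primary care and hospital". The method is in Main variables: "These three frailty parameters will be compared to each other to validate whether the FTS5 could be used as a practical and easy-to-apply tool". The Discussion repeats it as validation against Fried and the eFI and counts it as a key strength.

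The same section lists the components:
- FTS5: "1.- walking speed test, 2.- grip strength, 3.- Physical Activity, 4- Body Mass Index (BMI), and 5.- progressive Romberg test". A score above 25 of 50 counts as frail.
- Fried: "1.-weight loss, 2.-exhaustion, 3.-weakness, slowness, and 4.-low physical activity". Three or more criteria count as frail.
- eFI: built "using routinely collected electronic health record data (36 items) to quantify frailty".

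The Sample size section takes its inputs from FTS5-negative and FTS5-positive participants of an earlier cohort, with incident frailty as outcome. It concludes that "215 subjects in the exposed group and 1075 in the unexposed group are needed to detect a factor of risk" with a relative risk of 2.

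The Statistical analysis plan section gives a sequence: descriptive statistics, clustering, latent trajectory models, and then "the identified frailty phenotypes and patient clusters will be examined in relation to clinically relevant health outcomes". The outcomes listed are health care use, admissions, biomarker profiles and mortality.

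**The concern.** There are two linked problems.

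First, the only comparison with a power statement has no place in the analysis sequence. That section does not name FTS5, Fried or the eFI, and incident frailty is not among its listed outcomes. Conversely, none of the analyses it lists has a power statement.

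Second, the stated validation is a comparison of scales with one another, and one of the two comparators measures largely the same domains as the FTS5. Good agreement with Fried could then be read as evidence of validity when part of it comes from counting the same deficits twice.

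At stake is the claim that the FTS5 is fit for clinical use. It would rest on concurrent agreement, while the prognostic evidence the cohort was sized to give would have no pre-specified analysis. The Introduction itself cites prediction of adverse outcomes as support for the parent scale, so prognosis is a standard that the authors already use.

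**Working it through.** **1. The sample size figure.** Inputs from the Sample size section: p0 = 0.075 in FTS5-negatives; relative risk 2, so p1 = 0.15; two-sided alpha 0.05; power 80%; loss 10%; 1008/196 = 5.14 negatives per positive, and 1075/215 = 5.00 in the final numbers.

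Unpooled two-proportion formula, with k = 5 unexposed per exposed:

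n(exposed) = (1.960 + 0.842)² × [p1(1 − p1) + p0(1 − p0)/k] / (p1 − p0)²

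= 7.849 × [0.1275 + 0.069375/5] / 0.005625 = 7.849 × 0.141375 / 0.005625 = 197.3

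Allowing for loss, 197.3/0.9 = 219.2, so 220 + 1,100 = 1,320. The plan has 215 + 1,075 = 1,290, which is within 3%. The section names a Poisson approach, but the Poisson variants tried give 169 (log rate), 189 (score), 203 (square root) and 256 (Wald difference) exposed after loss, none of them within 3% of 215.

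**2. Is the size adequate for the contrast?** Power of 215 versus 1,075 at relative risk 2:

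| Test | Full numbers | After 10% loss |
|---|---|---|
| Pooled two-proportion | 90.5% | 87.7% |
| Poisson score | 87.4% | 84.3% |

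So the size is adequate, provided that these participants are all at risk of the outcome.

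**3. Sample size set beside the analysis.**

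| | Sample size section | Statistical analysis plan section |
|---|---|---|
| Exposure | FTS5-positive or negative | Data-derived phenotypes, clusters, trajectories |
| Outcome | Incident frailty | Health care use, admissions, biomarkers, mortality |

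Neither the exposure nor the outcome carries over.

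**4. Overlap of domains.**

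| FTS5 | Fried |
|---|---|
| Walking speed | Slowness |
| Grip strength | Weakness |
| Physical activity | Low physical activity |
| BMI | none (weight loss is a different criterion) |
| Progressive Romberg | none |
| none | Exhaustion |

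Three of five domains are shared, and three criteria are enough to be frail by Fried. For the eFI, the Introduction says only that the FTS5 variables "can also be incorporated into electronic tools, such as the electronic frailty index (eFI"). That does not make them eFI items.

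**5. A stylised illustration, not an estimate for this cohort.** Take two scores of five independent items with three in common and nothing else relating them, each dichotomised at about 16% positive (196/1,204 = 16.3%). Simulation with 400,000 draws gives:
- two continuous sums, shared items identical: correlation 0.60 (3/5), AUC 0.81, kappa 0.36;
- Fried as a count of binary criteria with cut-off 3, shared items identical: AUC about 0.76, kappa about 0.29;
- continuous sums, shared domains measured with correlation 0.7 (an assumption): AUC about 0.71, kappa about 0.23.

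The first case is the upper illustration. It treats both scales as sums of identically measured continuous items, which Fried is not.

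**6. The definition of the outcome.** The Sample size section does not say which scale defines incident frailty. Main variables makes an FTS5 score above 25 frail already. If positive means above 25, the outcome must come from another scale. If that scale is Fried, the overlap in step 4 enters the powered contrast as well.

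**The case against.** The strongest reply has four parts.

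- Comparison with two established measures is concurrent validation, a legitimate if partial form, and the eFI has no documented overlap with the FTS5. This stands. A reader might infer that the FTS5 is tested only against scales sharing its items, or that the validation aim cannot be answered. The documents support neither. FTS5, Fried, eFI, admissions and mortality are all to be collected, so the prognostic analysis is unplanned in the text rather than impossible.
- An article may leave the agreement statistic to a fuller plan. This also stands, and the lack of a named kappa or AUC is not part of the point. It does not remove the mismatch: the article sets out its analysis sequence, and the exposure and outcome in it differ from those that set the sample size.
- The earlier FTS5 data may be only planning inputs for a generic risk factor, and validation is secondary to the clusters. The wording of the sample size conclusion allows that reading. Even so, the only contrast described there is by FTS5 status, and no cluster analysis is tied to the calculation.
- Overlap is documented by domain, not by identical measurement, and a kappa of 0.2 to 0.35 would hardly pass as strong validity. This is fair. It is why the simulated values serve only as illustration and the argument rests on the component lists.

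**Conclusion.** The point holds in two parts. The contrast that sets the sample size has no stated analysis, although the size is adequate for it (84% to 88% power after 10% loss, on the plan's own inputs). The stated validation is mutual comparison, and agreement with Fried is partly built in because three of five domains coincide and those three can reach the cut-off alone. Agreement with Fried therefore cannot by itself establish validity; comparison with the eFI is not open to this objection on what the article documents.

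How much agreement the overlap adds in this cohort is unknown, since the article does not say how the Fried criteria are measured. The power figures assume 7.5% incidence, relative risk 2, a 5:1 split, and that all counted participants are free of the outcome at baseline. The change should be made: a named aim is affected, nothing is lost beyond recovery, and the Gantt chart lists data analysis as pending from 2028, so it can still be pre-specified.

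**What to change.** 1. Add the FTS5-positive versus FTS5-negative contrast on incident frailty to the analysis steps, among participants not frail at baseline. Name the scale that defines incident frailty and the FTS5 threshold that defines positive. State that a score above 25 already means frail and that a Fried-defined outcome carries the domain overlap. Correct the exposed/unexposed label on the 1008/196 ratio, which is glossed as negatives versus positives and so runs opposite to the final 215 exposed and 1,075 unexposed.
2. Add a head-to-head prognostic comparison of baseline FTS5, Fried and eFI in the same participants for all-cause mortality and non-elective admission. Report C-statistics with paired differences and 95% confidence intervals. Use Barthel decline only as a secondary outcome, because its ambulation, transfer and stair items overlap gait and balance. State that mortality and admissions are recorded beyond a diagnosis of frailty: the Abstract has annual collection of the clinical and laboratory data stop there, while the Statistical analysis plan section does not.
3. Report agreement between the scales as descriptive concurrent validity, and interpret agreement with Fried in the light of the three shared domains.

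The cost is a few more models and a few sentences of text, on variables already scheduled for collection. The result for the FTS5 may be less favourable than agreement alone would suggest.

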Plasma samples will be stored at −80 °C until analysis. For extraction, 10 μL of internal standard solution will be added to 100 μL of plasma, followed by 500 μL of cold acetonitrile (−20 °C) containing 1.5 M formic acid and 10 mM ammonium formate in the plate. After vortexing and incubation at −20 °C to induce protein precipitation, the extracts will be collected using a Waters Positive Pressure-96 processor (Waters, Milford, MA, USA), dried under a stream of nitrogen gas, and reconstituted in 100 μL of water:acetonitrile (80:20, v/v) containing 0.1% formic acid (v/v) and external standards. The samples will then be vortexed and prepared for injection.

Mass spectrometric analysis will be performed on a Sciex 7500 QTrap® instrument coupled with an Agilent 1290 UHPLC system. A Luna Omega Polar C18 column will be used for chromatographic separation, with distinct different gradients applied for positive and negative ion modes. The instrument will operate in scheduled MRM (sMRM) mode to ensure high sensitivity and selectivity for all targeted metabolites.

b)Clinical biomarkers assay

Plasma samples will be prepared and analyzed using a combination of direct flow injection tandem mass spectrometry (DFI-MS/MS) and liquid chromatography tandem mass spectrometry (LC-MS/MS) (20).

This targeted clinical biomarker assay will aim to provide a robust and user-friendly platform for the discovery and quantification of metabolomic biomarkers. The method will allow the targeted identification and quantification of up to 651 metabolites from 18 different analyte groups, including amino acids and derivatives, biogenic amines, organic acids, nucleotide/nucleosides, lipids, acylcarnitines, and glycerophospholipids. The analytical workflow will combine analyte derivatization, extraction and high-throughput quantification using MRM in tandem mass spectrometry. For accurate quantification, the method will incorporate stable isotope-labelled internal standards, along with other compound-specific internal standards, across all metabolite groups.

*Healthcare resource use:* Number of Primary Care consultations, prescribed drugs (polypharmacy), contacts with the Secondary Care facilities during the study period.

Non-elective hospital admissions and number of admissions and length of stay during the study period.

*All-cause mortality.*

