## Discussion

Frailty is, and will continue to be, one of the major challenges faced by our society, due to the growing ageing population and its profound implications for health systems and social care policies [15–17].

Although recent years have seen advances in the understanding and management of frailty, there is still limited knowledge regarding the events and mechanisms that drive the transition from robustness to frailty and, ultimately, to dependence.

From a scientific perspective, this project aims to generate valuable insights into the clinical and biological phenotypic clusters involved in the different stages of frailty. Additionally, it seeks to identify biological markers associated with frailty progression, allowing for earlier identification of at-risk individuals and monitoring of those prone to rapid deterioration. By uncovering these pathways, we hope to pinpoint potential therapeutic targets to improve patient management.

For this purpose, a prospective, multicenter, real-life cohort was designed to advance the understanding of frailty trajectories and their clinical impact. By combining clinical, functional, and biological data, the study aims to characterize phenotypic clusters of frailty and to elucidate mechanisms underlying disability progression. A key strength of the initiative is the validation of the FTS5 against established measures (Fried phenotype and eFI), assessing its feasibility and clinical applicability in both primary care and hospital settings. Furthermore, the creation of a biobank ensures long-term availability of biological samples for translational research.

The study’s comprehensive methodology—including annual follow-up, multidimensional assessments, and integration of metabolomic and biochemical data—provides an unprecedented opportunity to analyze frailty as a dynamic process rather than a static condition. Advanced clustering and longitudinal modeling will allow the identification of distinct trajectories and their correlation with clinically meaningful outcomes such as healthcare utilization, hospitalization, and mortality.

Overall, this study represents a significant step forward in frailty research by bridging population-based epidemiology, clinical practice, and biological mechanisms. Its design is expected to contribute not only to the refinement of diagnostic tools but also to the development of tailored preventive and therapeutic strategies for older adults at risk of disability.

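### A comparison of FTS5, Fried and eFI scores is used to show that FTS5 is practical and feasible in primary care and hospital, but it can show only agreement or validity

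*Protocol article*

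**What the plan says.** The protocol article gives FTS5 a practical purpose. The Introduction faults the full 12-item scale because it "takes about 15 minutes to complete, making it impractical in routine clinical settings where time is limited", and then states that "the project will validate the Frailty Trait Scale 5 (FTS5) as a practical and easily applicable tool" for primary care and hospital use.

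Under Main variables the method is fixed: the three frailty measures will be "compared to each other to validate whether the FTS5 could be used as a practical and easy-to-apply tool" in both settings. The Discussion counts the validation against Fried and eFI as a key strength, "assessing its feasibility and clinical applicability in both primary care and hospital settings".

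For FTS5 itself the article describes scores: "Each of the 5 domains scores from 0 (the lowest) to 10 (the highest), being 50 the highest score possible in this tool", with a total above 25 classed as frail. Under Study design and setting, "Participants are women and men over 65 years old who attend outpatient clinics at participating centers". Under Potential bias, every recruiting centre is said to have an outpatient clinic dedicated to frailty and older adults.

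**The concern.** Whether two instruments classify people alike and whether one of them can be used in a busy clinic are different questions, and they need different data. FTS5 could agree perfectly with Fried and still be too slow, need equipment that is not to hand, or often be left incomplete. It could also be quick and complete while agreeing poorly.

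If the stated plan is followed, the report will have agreement or validity results and will present them as evidence of practicality. A clinic or health service deciding whether to adopt FTS5 would then take a conclusion about time and ease of use from data that contain neither. The mention of primary care widens the gap, because the article describes no use of the scale there.

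**Working it through.** The article gives no figure for feasibility, so there is none to reproduce. The check sets the aim, the method, the recorded data, the analyses and the setting side by side.

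1. **Aim (Introduction, Main variables, Discussion).** Practicality, ease of application and feasibility, in primary care and in hospital.

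2. **Criterion the article itself uses (Introduction).** Completion time, with about 15 minutes judged too long for the full scale. Under Secondary variables an administration time is also given for the Lawton-Brody scale (10–15 minutes). None is given for FTS5, the tool whose case rests on brevity.

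3. **Method (Main variables).** Comparison of FTS5, Fried and eFI with each other. This yields concordance between classifications or correlation between scores. Linking scores to later events would add prognostic validity. Neither output is a function of how long the scale takes or why an item was not done.

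4. **Data listed (Main variables, Secondary variables).** Frailty scores, demographics, clinical history, questionnaires, DXA where available, blood tests, metabolomics, healthcare use and mortality. The resource-use item could be mistaken for a feasibility measure, but it is "Number of Primary Care consultations, prescribed drugs (polypharmacy), contacts with the Secondary Care facilities during the study period", which describes the patient's consumption of care and not the burden of giving FTS5. Administration time: not listed. Reason for an item not done: not listed. Item completion: not listed as an outcome, though derivable from the presence or absence of the five domain scores.

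5. **Analyses listed (Statistical analysis plan).** Description, clustering, latent trajectories, and a final step in which "the identified frailty phenotypes and patient clusters will be examined in relation to clinically relevant health outcomes". None concerns the feasibility of FTS5.

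6. **Setting (Study design and setting, Potential bias).** Outpatient clinics at six named centres, all with a frailty clinic. No primary-care site is named.

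7. **Opportunity left.** Study schedule: 1,500 planned. Last update: 500 recruited. 1,500 − 500 = 1,000 baseline visits remain if the target is met, plus later annual visits for all participants still in follow-up. Recruitment is open to the end of 2027. Precision would not be the obstacle. Even at the least favourable completion proportion (50%), the 95% half-width with 1,000 participants, ignoring clustering by centre, is 1.96 × √(0.5 × 0.5 / 1,000) = 0.031, or 3.1 percentage points. The obstacle is that time and reasons are not listed for collection.

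**The case against.** The strongest reply is that this is a condensed article. Timing fields and codes for items not done belong in a case report form or manual that is not shown, and the schedule figure is not shown either. That is fair as far as the absence of fields goes. It does not rescue the inference, because the article names the comparison of instruments as the route to the practicality conclusion, and that route fails whatever the forms contain.

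A second reply is that the words about practicality may only describe the kind of tool FTS5 is, with brevity taken as given (five items instead of twelve) and only measurement quality left to test. The sentence under Main variables could be stretched to that. The Discussion cannot, because it says feasibility and applicability are being assessed.

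Third, FTS5 validation is an addition to the main goal of building the cohort and finding phenotypic clusters, and no clustering, trajectory or outcome analysis depends on feasibility data. This stands and limits the importance of the point.

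A reader might also infer three stronger things that the documents do not support:

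- **That the study holds no information at all on feasibility.** The five domains are collected at baseline and at every later visit, so a crude completion proportion can be derived, including for those already enrolled.
- **That people unable to do the walking, grip or balance tests will become missing values and distort frailty prevalence.** The article does not say how an unperformed test is handled, and the domain scoring rests on a cited source. The exclusion of people with a Barthel Index below 60 or at the end of life should also reduce their number.
- **That adding timing fields would establish practicality in primary care.** Data from outpatient clinics at frailty-focused centres cannot do that.

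**Conclusion.** The point holds in this form: the article draws a conclusion about the practicality and feasibility of FTS5 in two settings from a comparison that can show only agreement or validity. By the article's own yardstick, time, the needed measure is not listed. Reasons for non-completion and a feasibility analysis are not listed either, and one of the two settings is not represented in the recruitment described.

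This affects a stated secondary aim and a claimed strength of the study. It leaves the clustering and trajectory work untouched and gives no reason to think that FTS5 is impractical. The conclusion rests on the text of the article, with the schedule figure and the data forms unseen. If those forms already record FTS5 time and reasons for non-completion, the remedy shrinks to describing them and stating the analysis, but the separation of aims and the limit on setting would still be needed.

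**What to change.** Under Main variables, state agreement and prognostic validity as one aim and feasibility as another. For feasibility:

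- record FTS5 administration time, and the reason for any item not done, at the remaining baseline and annual visits;
- report median time and the proportion with all five items complete, deriving completion as well for those already enrolled;
- confine the conclusions to the outpatient settings studied.

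If this is not wanted, restrict the Introduction, Main variables and Discussion to agreement and predictive validity, and drop the feasibility and primary-care claims.

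The first option costs some database fields and a note to sites, with no extra test or visit. It has two drawbacks. There will be no timing for the first 500 baseline visits. Also, gait, grip and activity overlap with the Fried criteria, so where a test is done once for both instruments, time must be recorded by item and not read off the whole visit. The second option costs only a change of wording.
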